### Participant timeline

The timeline for the study participants is shown in Fig. 1 and the enrollment, intervention and assessment schedule is shown in Table 1.

**Fig. 1 Fig1:**
[figure not shown]
Flow diagram of the trial. Exclusion criteria 12 and 13 are confirmed after informed consent, but before randomization. ICD: *International classification of disease*, DSM: *Diagnostic and Statistical Manual of Mental Disorders*

**Table 1 Tab1:** Schedule of the enrollment, intervention, and assessments

	Study periods							
		Enrollment	Allocation	Post-allocation				Close-out
	Timepoints	T_-1_	T_0_	T_1-A_	T_1-B_	T_2-A_	T_2-B_	T_x_^e^
Trial program	Enrollment							
	Screening	X						
	Randomization^a^		X					
	Intervention							
	Reminder A			X		X		
	Reminder B				X		X	
	Assessments							
	Baseline characteristics^b^	X						
Treating physician	Enrollment							
	PRIME-MD^c^	X						
	Eligibility assessment	X						
	Informed consent	X						
	Assessments							
	Lithium concentration^d^	X						X
	Liver function	X						X
	Kidney function	X						X
	Thyroid function							X

*PRIME-MD* Primary Care Evaluation of Mental Disorders

^a^Stratified block randomization will be conducted if the candidate has a measurement of serum lithium within 7 days of giving informed consent and an appointment between 4 and 8 months after giving informed consent

^b^Basic information includes gender, age, and concomitant medication

^c^The candidate will be classified as having major depression, bipolar I disorder, or bipolar II disorder

^d^Serum lithium will be classified into three groups (between 0.4 mEq/L and 1.0 mEq/L inclusive; < 0.4 mEq/L; or > 1.0 mEq/L)

^e^The first scheduled visit is between 18 and 24 months after informed consent

#### Screening by the trial program

The trial program automatically screens candidates who fulfill all of the following criteria from the EHR every morning:
Age ≥ 18 yearsHave active diagnostic codes of mood disorders (F30.x, F31.x, F32.x, F33.x, F34.x, F38.x, and F39.x) according to the *International classification of diseases* (ICD), 10th revisionFirst prescription of lithium carbonate more than 6 months previouslyLithium carbonate was prescribed more than twice in the previous 6 monthsNo serum lithium concentration measurement available within the previous 4 months

The algorithm that combined lithium prescription more than twice and the prescription period longer than 180 days ensure lithium continuation over 180 days, because the maximum prescription period is 90 days in Japan. The participant will not be screened if he/she has been already registered as “not eligible”, “refused participation”, or “withdrawal after participation”.

#### Eligibility check and registration

Primary Care Evaluation of Mental Disorders (PRIME-MD) is a semi-structured diagnostic tool to assist primary care physicians in the diagnosis of common mental disorders based on the DSM-5 [29]. The treating physician conducts the PRIME-MD and confirms the diagnosis of depression, bipolar I, or bipolar II. If the candidate meets the eligibility criteria and written informed consent is obtained, the treating physician registers the participant through the EHR. If the candidate is not eligible, refuses participation, or withdraws after participation, the treating physician enters the status through EHR. The treating physician will conduct a baseline blood test within 7 days of the patient giving informed consent. If the candidate does not receive the baseline blood test or a measurement of serum lithium is not available within 7 days, he/she will be excluded from the study.

### Sample size calculation

We estimated the sample size using Real World Data (RWD) database (Health, Clinic, Education, Information Evaluation Institute/Real World Data, Co., Ltd). Toyooka Hospital provides anonymized patient data to the database, which includes about 19 million patients’ data from 170 institutions in Japan. In RWD database, 1464 patients were prescribed lithium carbonate in a 6-month period. Of those, serum lithium was maintained between 0.4 mEq/L and 1.0 mEq/L in 818 (55.9%) patients. Although RWD database includes patients from Toyooka Hospital, the number of patients in Toyooka Hospital is unclear because numbers of patients in each hospital were not provided to the researcher.

In the trial, we assumed that 80% of participants in the intervention group and 55% of patients in the control group will achieve the goal. As 54 participants are needed for each group, assuming a dropout rate of 10%, a total of 120 participants is required to detect this difference with a type I error of 5% and a type II error of 10%, using the two-sided chi-square test.

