#### Primary outcome

The primary outcome is the achievement of therapeutic serum lithium concentration between 0.4 and 1.0 mEq/L at 18 months after informed consent. If a participant withdraws during the follow-up period or the result of the final blood test is not available, he/she will be regarded as not having achieved the primary outcome, because unavailability for the final serum lithium measurement strongly implicates that the patients is not adherent. However, the validity of this assumption will be tested in a sensitivity analysis using multiple imputation (see “Statistical analyses”).

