Second, in our sample size calculation with an EHR-based administrative database including Toyooka hospital, about 45% of patients had serum lithium of < 0.4 mEq/L or > 1.0 mEq/L. We assumed that the infrequent monitoring may partially have caused such deviation. Then, we expect that more frequent monitoring triggered by the reminders may be useful to maintain serum lithium within the appropriate range and achieve subsequent clinical outcomes. The two-step reminders (A and B) are to remind not only the physicians but also the patient. The reminders may, through the increased frequency of the reminder to the physician, the increased awareness on the part of the physicians, the increased recommendation from the physician to the patients based on such reminders, and/or through increased adherence on the part of the patients resulting from such interactions with the physician, help achieve the primary outcome of the therapeutic serum concentration. Then, it is not feasible to mask the patient, because we remind not only the physician to increase the frequency but also the patient to improve adherence. If the automated reminder system is found to be effective for achieving the appropriate serum lithium level in patients taking lithium carbonate in this study, this may contribute directly to improvement in the quality of clinical practice, because its implementation does not require additional effort by clinicians. On the one hand, the trial was so designed to pragmatically examine the net effect of this procedure and not to explore the mechanisms by administering additional questionnaires to the physicians and the patients. This may be a weakness but also a strength in increasing the practicality of the trial and also the generalizability of the final findings through facilitated recruitment.

Finally, both the EHR-nested RCT scheme and the EHR-nested automated reminder system may be applicable in medical specialties other than psychiatry. Overall, if the EHR-nested trial is successful, it can be expected to contribute to the so-called learning healthcare system, where every clinical encounter in routine care can provide an opportunity to expand the evidence base for future health care [31] (Additional file 1).

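### The 10% dropout allowance assumes dropouts leave the analysis, while the primary outcome scores most of them as failures; power is about 72% to 84% depending on the reading, not 90%

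*Protocol article*

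**What the plan says.** All references are to the protocol article.

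- **Sample size calculation.** The planning rates are stated as follows: "we assumed that 80% of participants in the intervention group and 55% of patients in the control group will achieve the goal". The error rates and test are given "with a type I error of 5% and a type II error of 10%, using the two-sided chi-square test". The total then follows: "As 54 participants are needed for each group, assuming a dropout rate of 10%, a total of 120 participants is required".
- **Primary outcome.** If a participant withdraws during follow-up "or the result of the final blood test is not available, he/she will be regarded as not having achieved the primary outcome". Multiple imputation is reserved for a sensitivity analysis.
- **Statistical analysis.** The primary outcome is analysed in the full analysis set on the intention-to-treat principle.
- **Stopping assessment.** Participants who withdraw consent to the protocol assessments, and those later found ineligible, are left out of the analyses.
- **Source of the control rate.** The sample size section gives 818 of 1464 database patients prescribed lithium (55.9%) as in range. The Discussion describes the remainder: "about 45% of patients had serum lithium of < 0.4 mEq/L or > 1.0 mEq/L".

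**The concern.** Inflating by 1/(1 − 0.10) protects power when dropouts disappear and about 54 evaluable participants per arm remain, still at 80% versus 55%. It does not do so when dropouts stay in the denominator as failures. In that case all 60 per arm are analysed, both success rates fall, and the difference between them shrinks. Nothing in the sample size section lowers the 80% and 55% for this.

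The document also gives two rules for people who leave. One scores withdrawals as failures; the other excludes those who withdraw consent to assessments. A reader cannot tell which rule the 10% allowance was meant to serve. At stake is how a null result would be read: the stated calculation implies a 10% chance of missing the assumed effect, and the true chance is larger on every reading.

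**Working it through.** **Inputs.** Rates 80% and 55%, two-sided alpha 5%, chi-square test, 54 then 60 per arm, 10% dropout (all from the sample size section). Allocation of 1:1 is implied by "54 participants are needed for each group". Equal dropout in the two arms is my assumption.

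**Formula (pooled variance).** With p̄ = (p1 + p2)/2,

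z = { |p1 − p2| − 1.96·√[2p̄(1 − p̄)/n] } / √{ [p1(1 − p1) + p2(1 − p2)]/n }, and power = Φ(z).

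**1. The plan's own figure.** For 80% versus 55%, the required number per arm is 72 at 90% power (71.7 before rounding up) and 54 at 80% power (53.9). So 54 does not reproduce at the stated 10% type II error; it reproduces exactly at 20%. The inflation step does reproduce: 54/0.9 = 60 per arm, 120 in total.

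**2. Dropouts excluded (54 analysed per arm, 80% vs 55%).** z = (0.25 − 1.96 × 0.0901)/0.0869 = 0.844, so power is 80.1%.

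**3. Dropouts scored as failures (60 analysed per arm).** Rates become 0.9 × 80% = 72.0% and 0.9 × 55% = 49.5%, a difference of 22.5 points. z = (0.225 − 1.96 × 0.0892)/0.0868 = 0.579, so power is 71.9%. Exact enumeration of the same test gives 72.4%.

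**4. 80%/55% already count missing as failure (60 per arm, no dilution).** z = (0.25 − 1.96 × 0.0855)/0.0824 = 1.000, so power is 84.1%. On this reading the inflation has no function.

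**5. Half the dropouts excluded, half scored as failures.** This leaves 57 per arm with 54 measured. Rates are 80% × 54/57 = 75.8% and 55% × 54/57 = 52.1%; power is about 75.6%.

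**6. Splitting the gap from 90%.** From 90% to 80.1% is about 10 points and comes from the base number of 54. From 80.1% to 71.9% is about 8 points and comes from the dropout handling.

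**7. Sensitivity of step 3 to the missing fraction, 60 per arm.**

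| Missing, scored as failure | Expected rates | Power |
|---|---|---|
| 5% | 76.0% vs 52.3% | 78.1% |
| 10% | 72.0% vs 49.5% | 71.9% |
| 15% | 68.0% vs 46.8% | 65.7% |
| 25% | 60.0% vs 41.3% | 53.8% |

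The last row is the low end of the 25–60% range that the Limitations section reports for some psychiatry trials.

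**8. Numbers needed under step 3 at 10% missing.** 73 per arm for 80% power and 97 per arm for 90%, with no further inflation.

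**The case against.** The strongest reply is that the protocol uses dropout in a narrower sense. The section on stopping the trial intervention says that someone who stops the intervention has not dropped out, and the next section removes from the analyses those who withdraw consent to assessments. If the 10% means that group, going from 54 to 60 is coherent and power is 80.1%. This stands as a possible reading. It does not remove the problem, because the primary outcome section scores participants who withdraw during follow-up as failures without exempting that group.

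The inflation could also cover losses between consent and randomisation, which are 4 to 8 months apart, since the article does not say whether the 120 are consented or randomised. That too gives at best about 80% with 54 per arm.

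A reader might infer that the trial simply has 72% power. The documents do not support that as an unconditional figure:

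- The sample size section does not say that all 1464 database patients had a measurement. The Discussion suggests it, by describing the rest as having out-of-range levels, but the source is not explicit.
- The factor 0.9 needs missingness that is equal across arms and unrelated to lithium level. The protocol's rationale for the failure rule is that missing tests signal non-adherence. If those missing would mostly have been out of range anyway, scoring them as failures costs less.

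A reader might also attribute the whole 18-point gap (90% to 72%) to dropout handling. That is wrong: about 10 points belong to the separate error in the type II rate.

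The Limitations section concedes that the 10% dropout and 25-point effect may be optimistic, and argues that trials with higher dropout differ from this one. That concerns the size of the assumptions. It does not address how dropouts enter the calculation.

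**Conclusion.** The point holds in conditional form. The dropout inflation does not match the missing-as-failure rule, and the document's two rules for withdrawals conflict. With 60 per arm enrolled and 10% missing, power is about 72% if all missing are failures, about 80% if all are excluded, and about 84% if the planning rates already include failures. The 72% rests on four assumptions: 80%/55% apply to measured participants; 10% are missing in each arm; missingness is unrelated to lithium level; and nobody is excluded for withdrawing consent to assessments. Above 10% missing, power under the failure rule is lower still.

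No reading delivers 90%. The part due to dropout handling is at most about 8 points at 10% missing. These figures use the chi-square test named in the sample size section; the planned covariate-adjusted logistic regression may differ somewhat.

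**What to change.** Keep the total of 120. Then:

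1. Reconcile the primary outcome and stopping-assessment sections, stating which participants who leave are analysed as failures and which, if any, are excluded.
2. State whether 80% and 55% count a missing final test as failure.
3. Replace the 1/(1 − 0.10) rationale with the expected rates for the endpoint as analysed. For example: with 80% and 55% among those measured, and 10% missing per arm scored as not achieved, the expected rates are 72.0% and 49.5%, and 60 per group gives about 72% power.
4. Report the range of about 72% to 84% over the readings above, and say that power is lower if more than 10% are missing.

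This changes wording only and leaves enrolment as planned. The downside is a visibly less favourable power statement.

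### The planned 54 per group gives 80% power for 80% versus 55%, not the stated 90%: at that number the risk of a false negative is twice the figure given

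*Protocol article*

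**What the plan says.** All inputs are in one paragraph of the protocol article, under Sample size calculation. On the rates: "we assumed that 80% of participants in the intervention group and 55% of patients in the control group will achieve the goal". On the number: "As 54 participants are needed for each group", which a 10% dropout allowance raises to 120 in total. The error rates and the test follow in the same sentence, where the 120 are "required to detect this difference with a type I error of 5% and a type II error of 10%, using the two-sided chi-square test".

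The Statistical analysis section agrees on sidedness: tests are two-sided with significance at p < 0.05. No other section gives a different power. Limitations concedes that the 10% dropout and the 25-point effect may be too optimistic, but does not question the type II error.

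**The concern.** Two proportions, a two-sided 5% chi-square test and a number per group together fix the type II error; it cannot be chosen separately. For 80% versus 55%, 54 per group is the familiar answer at 80% power, so the 10% beside it looks wrong.

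The stakes lie mainly in reading a null result. If the trial does not reach significance, readers will take it that a 25-point effect had a 90% chance of being detected. Limitations already warns that contamination between physicians may shrink the difference, and that the effect and dropout assumptions may be optimistic. Readers who discount for those warnings will start from 90% when they should start from about 80%.

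**Working it through.** **Inputs, all from Sample size calculation:** p1 = 0.80; p2 = 0.55; equal groups; two-sided alpha = 0.05 (z = 1.96); dropout 10%; stated type II error 10% (z = 1.2816). For comparison, a type II error of 20% has z = 0.8416.

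**Formula** (chi-square test, pooled variance under the null):

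n per group = [1.96 × √(2·p̄·(1 − p̄)) + z_beta × √(p1(1 − p1) + p2(1 − p2))]² / (p1 − p2)²

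- p̄ = (0.80 + 0.55)/2 = 0.675, and √(2 × 0.675 × 0.325) = √0.43875 = 0.6624
- √(0.16 + 0.2475) = √0.4075 = 0.6384
- (p1 − p2)² = 0.25² = 0.0625

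**Step 1: reproduce the plan's 54 and 120.** With a type II error of 20%: (1.2982 + 0.5373)² / 0.0625 = 3.369 / 0.0625 = 53.9, so 54 per group. Then 54 / 0.9 = 60 per group, 120 in total. Both stated numbers come out exactly.

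**Step 2: use the stated 10%.** (1.2982 + 0.8181)² / 0.0625 = 4.479 / 0.0625 = 71.7, so 72 per group. Then 72 / 0.9 = 80 per group, 160 in total.

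**Step 3: power at the stated number.** With 54 per group, (0.25 × √54 − 1.2982) / 0.6384 = (1.8371 − 1.2982) / 0.6384 = 0.844, which is 80.1% power and a type II error of 19.9%. Exact binomial enumeration of the uncorrected chi-square test gives 80.7%; with continuity correction it gives 74.7%. With 54 per group and 55% in the control group, 90% power is reached only at about 83% in the intervention group (83% gives 89.3%).

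**Step 4: does another method explain the 10%?** Number per group for 80% versus 55%:

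| Method | Type II error 20% | Type II error 10% |
|---|---|---|
| Two-sided, pooled | 54 | 72 |
| Two-sided, unpooled variance | 52 | 69 |
| Two-sided, arcsine | 54 | 72 |
| Two-sided, continuity-corrected | 62 | 80 |
| One-sided, pooled | 43 | 59 |
| One-sided, unpooled variance | 41 | 56 |

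No two-sided method comes near 54 at 10%. The closest value is the one-sided unpooled 56. It contradicts the stated two-sided test and leads to about 125 in total, not 120. A one-sided pooled test with 54 per group has 88% power. Using the database rate of 55.9% for the control group widens the gap: 58 per group at 20% and 77 at 10%.

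**Step 5: what if dropouts stay in the analysis?** The Primary outcome section counts a missing final lithium result as failure, so up to 60 per group may be analysed.

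- If 80% and 55% already include such failures: (0.25 × √60 − 1.2982) / 0.6384 = 1.000, power 84.1%.
- If they describe completers and 10% of each group fails by dropping out (an assumption): the rates become 0.9 × 0.80 = 72% and 0.9 × 0.55 = 49.5%, and power with 60 per group is about 72%.

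**The case against.** The arithmetic itself is hard to dispute; the fair objections concern its size and the remedy.

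- **The doubling depends on 54 analysed per group.** Because missing results count as failures, and Stopping assessment removes only those who withdraw consent to assessments or prove ineligible, the analysed number may be nearer 60. The type II error is then about 16% or 28%, depending on what the assumed rates describe. This stands as a qualification. But 54 is the number the protocol says it needs, and neither alternative reaches 90%.
- **The article does not say which figure is the slip.** It could be 10% written for 20%, or a real 90% intention with the wrong number. This also stands. The exact match of both 54 and 120 at 20% favours the first reading without proving it.
- **80% is the power of the planning calculation only.** The primary analysis is a logistic regression adjusted for diagnosis and baseline lithium, with missing counted as failure. That is correct, and the restated figure should be labelled accordingly.
- **A one-sided test with all 60 per group has 90.8% power.** This is the only combination examined with 60 or fewer per group that passes 90%, and it contradicts both the two-sided test and the stated need for 54.
- **Conduct, alpha and estimates do not change, and the confidence interval will inform readers too.** True, but power is a central design claim of a superiority trial, and the article states it wrongly.

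**Conclusion.** The stated type II error is wrong as written. For 80% versus 55% with a two-sided 5% chi-square test, 54 evaluable per group carries a type II error of 19.9%, twice the stated 10%. A true 10% needs 72 evaluable per group, which is 18 more per group, and 160 instead of 120 in total with the plan's own dropout allowance. Depending on how dropouts enter the analysis, two-sided power by the standard formula lies between about 72% and 84.1%. The 72% figure rests on the assumption that 80% and 55% are completer rates and that 10% drop out in each group. Everything else follows from figures in the article.

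**What to change.** In Sample size calculation, restate the type II error as 20% (80% power), keep 54 per group and 120 in total, and say that this is the power of the chi-square planning calculation with 54 evaluable per group. Use the same figure in the SAP, the registry entry and the results paper; the first two are not at hand, so check whether they repeat the 10%. The cost is one corrected sentence wherever the figure appears and a less favourable stated power. No extra patients are needed, and conduct and analysis do not change.

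If 90% power was the real intention, the number must change instead, to 72 evaluable per group and 160 in total, 40 more than planned. Trial status reports 101 recruited by 11 September 2019, with completion expected by 31 March 2020, so correcting the sentence is the proportionate course. The figures 54, 120 and 10% should not be left side by side.

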### Assignment of intervention

#### Randomization

The participants will be stratified into nine strata in accordance with the following two conditions in EHR, and automatically randomized by the trial program at their first scheduled visit between 4 and 8 months after informed consent, using permuted block randomization [30].
Diagnosis based on PRIME-MD (major depression, bipolar I disorder, or bipolar II disorder)Serum lithium (between 0.4 mEq/L and 1.0 mEq/L; < 0.4 mEq/L; or > 1.0 mEq/L)

#### Allocation sequence generation and concealment

Random allocation sequence is generated by an independent trial statistician (ST) but will not be notified to other researchers and participants. The allocation sequence is stored in the trial program and then concealed from other researchers.

### Masking

Allocation status will not be masked to the treating physician and the participant. Allocation status will be masked to the data manager, the trial statistician, and the steering committee until the steering committee finalizes the interpretation report with masked data.

